### Primary outcomes

The primary outcome of the study will be a judgment about the feasibility of conducting a full-scale RCT. The specific aspects of feasibility that will be monitored are listed below.

#### Integrity of the study protocol

Here, integrity includes the appropriateness of the inclusion criteria, the training of the staff, clinic accessibility for the subjects, the acceptability of the intervention by the subjects and therapists, and the time and facilities required to deliver the interventions. These data will be gathered from interviews with the subjects and therapists.

#### Recruitment and retention

The goal is to enroll at least 80% of the eligible subjects recruited. Once the subjects are enrolled, the goal will be that at least 80% of the subjects attend at least 75% of the treatment sessions and complete at least 75% of the prescribed exercises.

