**Methods:**

The protocol describes a randomized controlled pilot trial with 40 subjects divided into study and control groups. Both groups will receive 8 weeks of PSSE, but the study group will also receive spinal manipulative therapy during the first 2 weeks before PSSE. The primary outcome will be an estimate of the feasibility of conducting a full-scale experiment. The influencing factors will be the time to complete enrollment, the recruitment rate, subject retention, and adherence to the treatment allocations. The secondary outcomes that will be used to assess the efficacy of treatment will include the Cobb angle, somatosensory evoked potentials, ATR, three-dimensional postural parameters, and scores on the 22-item Scoliosis Research Society outcomes questionnaire. The Cobb angle will be measured at baseline and at the end of 8 weeks of training. The somatosensory evoked potentials will be measured at baseline and at the end of 2 weeks of training. The ATR, three-dimensional postural parameters, and scores on the 22-item Scoliosis Research Society outcomes questionnaire will be measured at baseline and at 2 weeks, 4 weeks, and 8 weeks of treatment.

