### Intervention

#### Physiotherapeutic scoliosis-specific exercises

Each subject will undergo outpatient PSSE under the supervision of therapists during 30 min sessions, 5 times per week, for 4 weeks; then, they will undergo another 4-week home-based PSSE regimen implemented under the supervision of their parents, with 30-min sessions performed 5 times a week. The PSSE will include autocorrection in three dimensions, stabilization of the corrected posture, training related to activities of daily living and patient education [35]. The PSSE program will be developed based on the work of Schroth [36, 37] and on the scientific exercise approach to scoliosis [38]. Three-dimensional active correction involves correcting the curvature in the coronal plane, rotation in the horizontal plane, and abnormal physiological curvature in the sagittal plane at the same time. During training, the individuals gradually transition from lying to sitting, and finally to standing. A balance pad or wedge pad will be used for correcting the lateral curvature or hump, and an elastic band will be used to help stabilize the subjects in the corrected posture. Rotational breathing will be involved to correct vertebral rotation as well as asymmetry in the thorax [19]. The subjects will be trained to draw in air to the concave side when inhaling and to expel air first from the convex side when exhaling. At the beginning, the therapists will use their hands to guide the subjects to inhale or exhale correctly. As the subjects become more skilled, breathing under supervision will continue to be required. Meanwhile, the therapists will instruct the subjects on how to integrate their exercises into their daily activities, such as standing and sitting. It will also be necessary to educate the subjects and their parents about the types of scoliosis, possible hazards, and the risk of progression. The PSSE will be guided by two therapists with more than 4 years of experience in the treatment of scoliosis. Some PSSE examples are shown in Fig. 3.

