#### Spinal manipulative therapy

In the first 2 weeks, the study group will additionally receive SMT before PSSE 5 times a week. SMT will involve 5 min of evaluation, 10 min of soft tissue relaxation techniques, and 15 min of HVLA manipulation.

Before SMT is performed, it is necessary to evaluate and find the dysfunctional spine segments. Pain and tenderness during palpation or the examination of local tissue are the primary indicators used for identifying the dysfunctional segments [39]. Restricted joint mobility during the spinal examination is also an important indicator [39]. In this study, if the physiotherapist finds any pain, tenderness, or restricted joint mobility when assessing the region from C7 to S1 and the sacroiliac joints, the segments involved will be defined as dysfunctional and recorded as target segments for treatment. For thoracic and lumbar segments, the alignment of the spinous processes is assessed with unilateral or bilateral fingertip contacts. Any potential tenderness or pain around the spinous processes and soft tissues will be recorded. In addition, coupled lateral flexion and rotation movements will be induced on both sides in the extended and flexed positions. For example, the examiner will stand on the subject’s left side, place his right thumb on the right thoracic spinous process, and guide the subject’s upper body with his left hand from a neutral and upright sitting position into rotation and lateral flexion position until the movement reaches the palpating thumb. During the examination, if the subject complains of pain or the examiner observes asymmetric motion between the left and right sides, that means the segments are dysfunctional. For the sacroiliac segments, the subjects will stand barefoot on a firm surface, and the therapist will first palpate the posterior superior iliac spine on both sides and assess the asymmetry as well as the presence of any pain or tenderness during palpation. The positions of the bilateral sacroiliac joint surface projections will be assessed at the same time. The evaluation procedure will be based on that described in chapters 9 to 11 of the palpation techniques book: surface anatomy for physical therapists [40].

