### Assessment

Age, sex, height, weight, Risser sign, menarche status (for the girls), and type of scoliosis will be recorded at the start of the experiment. The United States Risser staging will be used to quantify skeletal maturity on a scale of 0 to 5 [43]. Stage 0 represents no ossification of the iliac apophysis, whereas stage 5 represents complete ossification and fusion. The scoliosis types will include thoracic, lumbar, thoracolumbar, and S-shaped scoliosis, corresponding to the anatomical site of the spinal deformity [1].

The primary outcome will be the feasibility of performing a full-scale study using these protocols. The time to complete enrollment, recruitment rate, subject retention, and adherence to the treatment allocation will all be important observations. The efficacy of treatment will be the secondary outcome. Spine curvature, rotation of the trunk, and postural symmetry will be assessed by the Cobb angle from X-ray images; the ATR, as measured with a Scoliometer; and 3-DPPs, as measured using a global postural system (GPS), respectively. The SEP will be assessed for evaluating sensorimotor integration, and the SRS-22 will be administered for the quality of life. The Cobb angle will be measured at baseline and at the end of 8 weeks of training. The SEP will be measured at baseline and at the end of 2 weeks of training. The ATR, 3-DPPs, and SRS-22 scores will be measured at baseline and then after 2 weeks, 4 weeks, and 8 weeks of treatment. The mean changes of Cobb angle from baseline to the end will be compared. And the mean difference of other indicators between each two visits will be used for comparative analysis.

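### The adherence goal for the primary feasibility outcome has no threshold for SMT, for each arm or for the week-8 assessment, so it can be met when these fall short

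*Protocol article*

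**What the plan says.** Under Recruitment and retention, the protocol article asks that, once enrolled, "at least 80% of the subjects attend at least 75% of the treatment sessions" and "complete at least 75% of the prescribed exercises". It does not define which sessions count, and it does not separate the arms.

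The schedule is in the Intervention section. Every subject has supervised exercise (PSSE) "during 30 min sessions, 5 times per week, for 4 weeks". After that, "they will undergo another 4-week home-based PSSE regimen implemented under the supervision of their parents", "with 30-min sessions performed 5 times a week". In the first 2 weeks "the study group will additionally receive SMT before PSSE 5 times a week".

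The Abstract lists "subject retention, and adherence to the treatment allocations" among the factors that determine feasibility, and the Assessment section repeats both. The statistical analysis section says that the primary outcome measures will be read against the pre-set goals. On the X-ray, the Assessment section says: "The Cobb angle will be measured at baseline and at the end of 8 weeks of training".

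**The concern.** Adherence to the allocated treatment and retention are both named as parts of the primary outcome, but the one numerical goal measures neither directly. PSSE is common to both arms and supplies most of the sessions, so good PSSE attendance can mask poor SMT delivery. Good adherence among controls can mask poor adherence in the study group. The goal is a share of sessions and not a completed assessment, so a subject can satisfy it and still leave before the only post-baseline Cobb angle.

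At stake is whether the pilot's yardstick would show the failures that matter most for a full-scale trial: the treatment contrast not delivered, or the Cobb outcome not collected. The change in Cobb angle is the variable behind the sample size and the interim analysis.

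**Working it through.** **The plan's own figure.** With d = 1.0, two-sided alpha 0.05 (two-sidedness assumed) and 80% power, the two-sample t test needs n = 16.7, so 17 per group (power 80.7%). Allowing for 15% dropout, 17 / 0.85 = 20 per group, 40 in total. The stated sample size reproduces. It presumes 34 of 40 subjects with a Cobb change.

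**Session counts, from the Intervention section.** Supervised PSSE 5 × 4 = 20; home PSSE 5 × 4 = 20; SMT (study group only) 5 × 2 = 10.

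**Fewest SMT sessions with which a study-group subject reaches 75%, all PSSE attended:**

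| Sessions counted | Total | 75% needs | Fewest SMT |
|---|---|---|---|
| SMT + all PSSE | 50 | 38 | 0 (40/50 = 80%) |
| PSSE sessions or training days | 40 | 30 | 0 |
| SMT + clinic PSSE, counted separately | 30 | 23 | 3 (20 + 3 = 23; 77%) |
| Clinic visits, SMT at each attended visit | 20 | 15 | 5 (15 − 10 visits in weeks 3–4) |
| SMT alone | 10 | 8 | 8 |

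On the clinic-visit count the minimum falls to 0 if SMT is withheld at visits that are attended.

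**Arms taken together.** 80% of 40 = 32, and 32 − 20 controls = 12, so 8 of 20 study subjects (40%) may fall short. If those 8 received no SMT and the 12 received the minimum, the share of the 20 × 10 = 200 planned SMT sessions delivered would be 12 × 0 / 200 = 0%, 12 × 3 / 200 = 18%, 12 × 5 / 200 = 30% or 12 × 8 / 200 = 48%.

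**Chance of meeting the goal.** The true adherence rates below are assumptions; the article gives none. Let X ~ Bin(20, study rate) and Y ~ Bin(20, control rate), independent. The pooled goal is P(X + Y ≥ 32); a study-arm goal is P(X ≥ 16).

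| Control rate | Pooled, study rate 60% | Pooled, study rate 70% |
|---|---|---|
| 80% | 10.5% | 29.8% |
| 85% | 17.9% | 43.7% |
| 90% | 28.5% | 59.4% |
| 95% | 42.6% | 75.2% |
| *Study-arm goal 16/20* | *5.1%* | *23.8%* |

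**Leaving before week 8.** 75% of 40 exercise sessions = 30, reached at the end of week 6 (30 / 5) with full attendance. By then the subject has 20/20 supervised sessions and, in the study group with full SMT, 30/30 clinic sessions or (10 + 30)/50 = 80% of all sessions. If the exercise condition refers to home sessions only, 75% of 20 = 15, reached after 3 home weeks, at the end of week 7. On either count the goal is met without a week-8 X-ray.

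**The case against.** A reader might infer that the goal is met with at most 3 of 10 SMT sessions however sessions are counted. The article does not support that. It separates attending sessions from completing exercises, and home training is not naturally attended, so counting the 20 clinic visits is a fair reading. If SMT is given at each attended visit, at least 5 of 10 are then needed. Because SMT immediately precedes PSSE, full PSSE attendance with almost no SMT requires SMT to be refused or withheld. The Adverse events section does foresee discontinuing SMT for persisting discomfort, and following that provision is not non-adherence. This part of the objection stands.

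A reader might also infer that the goal by itself returns a finding of feasible. It does not. The Primary outcomes section calls feasibility a judgment over several aspects, including interviews on acceptability and delivery. Retention and adherence to allocation are also listed as observations in their own right, so poor SMT delivery or missing X-rays could still come to light. The article does not forbid tabulation by arm, and a fuller document may provide it.

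The size of the pooling effect depends heavily on the assumed control adherence: at 80% among controls, the pooled goal is only modestly easier than the study-arm goal.

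The objection does not remove the core of the point. The goal is stated, the article makes such goals the standard for interpretation, and it contains no limit for two components that the article names as primary.

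**Conclusion.** The point holds as a weakness in a stated rule and should be fixed. It does not show that the feasibility judgment must go wrong.

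How much SMT a passing subject may miss depends on an undefined term: the minimum is 0, 3 or 5 of 10 sessions on the counts considered, and 8 only if 75% is applied to SMT alone, which the text does not say. The other two gaps do not depend on how SMT is counted. Taken over all subjects, the goal tolerates 8 of 20 study subjects falling short, and it is met by a fully attending subject who leaves after week 6 or 7 without a week-8 Cobb angle.

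Under assumed control adherence of 80% to 95%, the pooled goal is met 11% to 43% of the time at 60% study-arm adherence (5% for 16/20) and 30% to 75% at 70% (24% for 16/20). These figures treat subjects as independent. The sample size is unaffected. How much SMT is clinically adequate is not judged here.

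**What to change.** Keep the 80% and 75% limits and revise the goal as follows:

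- State which sessions count, and report and judge attendance and exercise completion separately in each arm.
- Add a study-arm goal: at least 80% (16/20) receive at least 75% of the scheduled SMT sessions (8 of 10, since 7.5 rounds up). Report SMT discontinued under the Adverse events section separately.
- Add a retention goal: at least 85% (34/40) have the week-8 Cobb X-ray, matching the 15% dropout in the Sample size section.

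The limits reuse the protocol's own percentages. Home check-ins are already collected. The article does not explicitly describe a log of clinic and SMT attendance, so one should be confirmed.

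The costs are real. The goals become harder to meet, and 16/20 is imprecise: with true adherence of exactly 80% it is met only 63% of the time. Recruitment was under way, so the change must be documented as an amendment to the pre-set goals.

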#### Randomization procedure

The appropriateness of the methods used to ensure the blinding of the assessor and the statistical analyst will be determined through post-study interviews in which these individuals will be asked whether they were aware of the group allocation results and whether they felt that the security protocols were reliable.

#### Primary outcome measure

Selection the most appropriate primary outcome measure for a full-scale RCT will be determined using the secondary outcome measures with the largest between-group effect size.

#### Sample size calculation

The sample size needed for a full RCT will be estimated using the effect-size data from this pilot study.

### Secondary outcomes

#### Cobb angle

The Cobb angle will be measured using a standing, full-spine X-ray image in the anteroposterior view. The most tilted vertebrae above and below the curve will be determined first. These vertebrae will be those where the endplates are most tilted towards each other [44]. The angle between the intersecting lines drawn perpendicular to the top of the top vertebra and the bottom of the bottom vertebra will be measured as the Cobb angle.

#### Somatosensory evoked potentials

According to previous studies, the dual peripheral nerve stimulation SEP technique may be a sensitive measure of sensorimotor integration for musculoskeletal disorders [45, 46]. Our research will follow Haavik-Taylor’s protocol [46] for the collection and analysis of SEP in the upper limbs, especially regarding the parameters of the dual stimulation of the median and ulnar nerves.

All subjects will undergo SEP assessment twice at baseline and at least 6 h after the last treatment session after 2 weeks of training. In each assessment, three SEP trials (average 1000 sweeps) will be carried out in a random order, including the stimulation of the median nerve individually (M), stimulation of the ulnar nerve individually (U), and simultaneous stimulation of both nerves (MU). The stimuli consist of electrical square pulses that are 1 ms in duration and delivered at a rate of 2.47 Hz, at the motor threshold. All the stimulating electrodes, recording electrodes and their reference electrodes will be placed according to the recommendations of the International Federation of Clinical Neurophysiologists (IFCN) [47]. During the recordings, the lights in the room will be dimmed, and the subjects will be asked to lie supine on the bed with their limbs relaxed and eyes closed.

According to the recommendations of IFCN, the SEP amplitudes will be measured from the peak of interest to the preceding or succeeding trough. The SEP latencies will be measured at the peak of the waveform of interest. The amplitudes and latencies of peripheral N9, spinal N11 and N13, far-field P14 and N18 potentials, parietal N20 (N20–P25 complex), and frontal N30 (P22–N30 complex) will be identified and analyzed. In addition, the MU/M + U SEP peak ratios will be calculated. An assessor with 4 years of experience using the EMG equipment will complete all the subjects’ assessments.

#### Angle of trunk rotation

A Scoliometer (Fabrication Enterprises Inc., New York, USA) will be used to quantify the degree of rotation of the trunk. The subjects will be instructed to slowly bend forward to approximately 90° with their feet together, knees straight, arms dangling, and hands together [48]. The Scoliometer will be centered on the spinous process and placed vertically in the most obviously deformed part of the subject’s back. The therapist will ensure that the subject’s back is horizontal and then record the angle of trunk rotation.

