### Randomization and blinding

The physician will explain the whole content of the trial to the candidates who meet the eligibility criteria in a separate room. Written informed consent from both subject and their statutory guardians are required. Their demographic information and medical history will then be recorded.

Each subject will be assigned to either the study or the control group using simple randomization with a 1:1 allocation. The random sequence will be generated by an investigator using an electronic random sequence generator (www.random.org). The numbers in the random sequence will be sealed in consecutively numbered, opaque envelopes. When required, the envelopes will be opened by a person who will not be involved in the intervention, assessment, or statistical analysis.

Due to the nature of the interventions, blinding of the therapists and subjects to the intervention type will be impossible, so only the assessors and those performing the statistical analysis be blinded to the allocation results. To ensure that the group allocation results remain concealed as much as possible, the assessors will process the assessments in a separate room, and the statistical analysis will not include the information about the subjects and their allocations. The schedule for the treatments and outcome assessments is presented in Fig. 2.

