##### Posture parameter analysis

The images will be processed by the GPS system’s software to measure the angles and distances between the markers. Estimates of the sagittal head angle, craniovertebral angle, protracted shoulder angle, shoulder alignment, scapula asymmetry, right and left waist angle, frontal pelvic tilt, sagittal pelvic tilt right, C7 alignment, and S1 alignment will be generated. Fortin’s method [50] will be used to calculate the angles and distances*.* Some details are shown in Additional file 3.

The same assessor with 4 years of experience using the GPS equipment will complete all of the subject assessments. The reliability and validity of this device has been verified in previous studies [51, 52].

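### The angle of trunk rotation is recorded by the therapist, a role the protocol says cannot be blinded, and nothing says this person is a separate, blinded assessor

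*Protocol article*

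**What the plan says.** The Randomization and blinding section sets a rule for the whole trial. It says that "blinding of the therapists and subjects to the intervention type will be impossible". Blinding is therefore confined to two roles, the outcome assessors and the analysts. To protect this, "the assessors will process the assessments in a separate room". No outcome is exempted.

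The Angle of trunk rotation section describes a hand-held Scoliometer reading. The device is to be "placed vertically in the most obviously deformed part of the subject’s back". The section then says: "The therapist will ensure that the subject’s back is horizontal and then record the angle of trunk rotation".

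Two other outcome sections use a different word for the person who measures. For the evoked potentials: "An assessor with 4 years of experience using the EMG equipment will complete all the subjects’ assessments". For the three-dimensional postural parameters (3-DPPs): "The same assessor with 4 years of experience using the GPS equipment will complete all of the subject assessments".

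ATR is a secondary efficacy outcome, measured at baseline and at 2, 4 and 8 weeks (Assessment). The secondary outcome with the largest between-group effect size is to guide the choice of primary outcome for the full trial (Primary outcome measure). ATR is also among the outcomes used to plan that trial's sample size (Data collection, data management, and statistical analysis).

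**The concern.** Read literally, the ATR section gives the recording of an efficacy outcome to a role that the protocol itself declares unblinded. The measurement leaves room for judgement: where the deformity is greatest, whether the device is centred, whether the back is horizontal, and what the angle is. An observer who knows the arm could shade any of these without meaning to.

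Three things would be at stake.

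- **Choice of outcome.** A shift in favour of the manipulation arm would make ATR more likely to show the largest effect size, and so to be picked as the full trial's primary outcome.
- **Sample size.** The same shift would enter the ATR effect size carried into planning. An inflated effect would make the full trial too small.
- **The feasibility verdict on blinding.** Under Randomization procedure, the adequacy of blinding is one of the pilot's own primary feasibility aspects. It is judged by interviewing the assessor and the statistical analyst. If a therapist records ATR, both interviews could report sound blinding while one outcome was read unblinded.

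**Working it through.** The point rests on comparing sections. No figure in the protocol depends on it.

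**1. Who is blinded.** Randomization and blinding: therapists no, subjects no, assessors yes, analysts yes.

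**2. Who measures what.**

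| Outcome | Person named | Section |
|---|---|---|
| Evoked potentials | an assessor | Somatosensory evoked potentials |
| 3-DPPs | the same assessor throughout | Posture parameter analysis |
| ATR | the therapist | Angle of trunk rotation |
| Cobb angle | nobody named | Cobb angle |

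**3. What therapist means elsewhere.** The exercise and manipulation sections use it for those who deliver treatment, and the Adverse events section for the person who telephones subjects. Monitoring and auditing lists physiotherapists and assessors as separate members of the board. Integrity of the study protocol interviews therapists, while Randomization procedure interviews the assessor. No section describes a therapist who only assesses and is kept blind.

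**4. Which ATR steps are given to the therapist.** Two: ensuring that the back is horizontal, and recording the angle. The instruction to bend and the placement of the Scoliometer are in the passive voice, with no person named. The two named steps are enough to expose the reading to expectation.

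**5. How often.** There are four visits, three of them after baseline, so the exposure recurs at 2, 4 and 8 weeks.

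**6. The stated sample size, for reference.** The Sample size section uses the Cobb angle, d = 1.0, a 5% level and 80% power. For a two-sample t test with n per group, df = 2n − 2 and noncentrality d·√(n/2). Taking the test as two-sided, power is 0.781 at n = 16 and 0.807 at n = 17, so 17 per group reproduces. Allowing for 15% dropout, 17/0.85 = 20 per group, 40 in total. The ATR point leaves this unchanged.

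**7. Scale only, on assumed shifts.** The protocol gives no ATR SD, reading error or direction of bias. Suppose there is no true effect and unblinded reading shifts the between-group ATR change by b SD. The standard error of a standardized difference with 17 per group is about √(2/17) = 0.34. A simple two-sided 5% t test (df = 2n − 2, noncentrality b·√(n/2)) would then reject in:

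| Assumed b (SD) | 17 per group | 20 per group |
|---|---|---|
| 0 | 5.0% | 5.0% |
| 0.1 | 5.9% | 6.1% |
| 0.2 | 8.7% | 9.5% |
| 0.3 | 13.6% | 15.2% |
| 0.5 | 29.3% | 33.8% |

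The plan analyses ATR by repeated-measures analysis of variance, so the t test is a simplification. The table shows what a shift would do if there were one. It is no evidence that one exists.

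**The case against.** The best reply is that the word is a loose job title. The blinding rule covers all assessors and exempts no outcome. The ATR section describes technique and does not assign staff, and it does not say that the person treats the subject. In a rehabilitation department a blinded assessor may well be a therapist by profession. The contrast with the other outcomes is also weaker than it looks. Those sections name an assessor to state experience with the equipment, and neither calls that person blinded, so their blinding rests on the same general rule.

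This stands as a plausible reading, and it limits the claim. It does not remove the inconsistency. The document nowhere supports that reading, and a site following the ATR section to the letter could have a treating therapist take the measurement.

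The reply on importance stands too. The primary outcome of this pilot is feasibility, and ATR is one of five secondary efficacy measures. The sample size and the interim efficacy stop both use the Cobb angle, so no efficacy decision inside this trial depends on ATR. Its influence is on the planning of the full trial, where it is one candidate among several.

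A reader might go further and infer that the protocol plans unblinded ATR assessment, that the therapist also places the device, or that the ATR comparison is therefore biased. The text supports none of these. It leaves the blinding of the ATR reader unresolved, names nobody for placement, and gives nothing from which a bias could be shown or sized.

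**Conclusion.** The inconsistency is real. One section has the therapist record ATR, another says therapists cannot be blinded, and no section reconciles the two. As written, an observer-dependent outcome could be read unblinded at each of the three post-baseline visits. That could bias the ATR effect size used to choose the full trial's primary outcome and sample size, and the planned blinding interviews could miss it.

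The conclusion rests on the word being used here as it is elsewhere in the protocol. If it means a blinded assessor, the fault is one of wording only, and the correction is still needed. The size of any bias cannot be estimated from the document, and the illustrative rejection rates depend entirely on assumed shifts.

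This should be fixed. Calling it essential to the trial's validity would be too strong for one secondary outcome in a feasibility pilot.

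**What to change.** Reword the Angle of trunk rotation section so that one blinded assessor, not involved in treatment, positions the subject, places the Scoliometer, and reads and records the angle. The assessor who measures the 3-DPPs is a natural choice, because both outcomes are due at the same four visits. The protocol gives that person's experience with the postural system only, so Scoliometer training would have to be confirmed or provided.

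Recruitment is described as ongoing (Trial status), so establish who has taken the readings so far. Report any taken by a treating therapist as unblinded, and interpret the ATR effect size accordingly when planning the full trial. Include whoever measured ATR in the post-study blinding interviews.

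The cost is a change of wording and a few minutes of assessor time per visit, plus any training needed. The sample size does not change.
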